## LIST OF ABBREVIATIONS

| Term   | Definition                                |
|--------|-------------------------------------------|
| 3-D SI | 3-dimensional 180° camera surface imaging |
| AE     | Adverse Event                             |
| NCI    | National Cancer Institute                 |
| TMHRI  | The Methodist Hospital Research Institute |

## STUDY SYNOPSIS

|                                     |                                                                                                                                                                                                                                                                                                                                                                                                                                                                                                                                                                                                                                                                                                                                                                                                                                                                                                                    |
|-------------------------------------|--------------------------------------------------------------------------------------------------------------------------------------------------------------------------------------------------------------------------------------------------------------------------------------------------------------------------------------------------------------------------------------------------------------------------------------------------------------------------------------------------------------------------------------------------------------------------------------------------------------------------------------------------------------------------------------------------------------------------------------------------------------------------------------------------------------------------------------------------------------------------------------------------------------------|
| SPONSOR:                     | The Methodist Hospital Department of Surgery                                                                                                                                                                                                                                                                                                                                                                                                                                                                                                                                                                                                                                                                                                                                                                                                                                                                       |
| TITLE:                       | A Pilot Study for the Identification of Targets for Clinical Improvement in Breast Conserving Therapy                                                                                                                                                                                                                                                                                                                                                                                                                                                                                                                                                                                                                                                                                                                                                                                                              |
| OBJECTIVES:                  | 
The primary objective of this study is
 
 
to compare the surgical lumpectomy, lumpectomy healing process and surface contour changes to the predicted multiscale model to characterize
 
 
Secondary objectives include:
 
 
provide information regarding the use of 3-dimensional surface imaging to detect changes over time in the skin surface and dimension related to lumpectomy healing and breast contour
 
provide information on the use of ultrasound of the lumpectomy bed and changes that occur during the course of breast cancer treatment and healing
 
to describe the course of pain experienced by women undergoing BCT and the correlation of pain to the healing process.
 
provide information on the use of thermal Imaging to capture changes during healing
 
 |
| TRIAL DESIGN:                | The proposed study is a single-center, prospective, pilot, observation study to tabulate and measure the changes that occur during treatment and healing for breast conserving therapy (BCT) in women with non-metastatic breast cancer for comparison to the multiscale model of breast lumpectomy and healing in order to identify targets for improving BCT.                                                                                                                                                                                                                                                                                                                                                                                                                                                                                                                                                    |
| TYPE AND NUMBER OF SUBJECTS: | The study will be comprised of 12 de novo breast cancer patients with non-metastatic breast cancer undergoing BCT.                                                                                                                                                                                                                                                                                                                                                                                                                                                                                                                                                                                                                                                                                                                                                                                                 |
| Main Inclusion criteria      | 
 
Adult females <math>\geq</math> age 30 years
 
Have early stage (Stage I, II), non-metastatic breast cancer
 
Planned to receive BCT
 
Have received a pre-operative mammogram within 30 days of surgery
 
Have received pre-operative magnetic resonance imaging (MRI) within 30 days of surgery
 
Planned to receive post-surgery radiotherapy, by whole breast radiotherapy
 
                                                                                                                                                                                                                                                                                                                                                                                                                                                |

|                                      |                                                                                                                                                                                                                                                                        |
|--------------------------------------|------------------------------------------------------------------------------------------------------------------------------------------------------------------------------------------------------------------------------------------------------------------------|
| Main Exclusion criteria       | 
 
• Adult females younger than 30 years of age
 
• Previous breast cancer
 
• Neo-adjuvant therapy for breast cancer
 
• Participation in a study of investigational drug in the previous 30 days
 
 |
| TRIAL AND TREATMENT DURATION: | Subjects will be enrolled in the study during the 3 weeks prior to receiving their BCT surgery and will be followed for six months after the BCT surgery. A total of 6 visits (not including the surgery) are planned.                                                 |

## Background and introduction

Breast cancer is the most common cancer of women in the world; it is estimated that 470,000 women died of breast cancer in 2008. Improving breast cancer treatment outcome and survival depends on early detection and effective use of multimodality therapy: surgery, radiation oncology, and medical hormonal and chemotherapy treatments. Surgery for early stage breast carcinoma is either total mastectomy (complete breast removal) or surgical lumpectomy (tumor removal) with radiation therapy, commonly known as Breast Conserving Therapy (BCT). The goals of BCT are to achieve local control of the cancer as well as to preserve a breast that satisfies the woman's cosmetic emotional and physical needs. While most women undergo partial mastectomy with satisfactory cosmetic results, in many patients the remaining breast is left with significant cosmetic defects including concave deformities, distortion of the nipple-areola complex, asymmetry and changes in tissue consistency characterized by excessive density associated with parenchyma scarring. These flaws have been reported to contribute to poor body image and psychological distress in some patients. Research efforts to improve the surgical outcomes of BCT in regards to prediction of cosmetic and functional outcome are very limited.

There are currently no tools, other than surgical experience and judgment that can optimize cosmetic outcome or predict the impact of partial mastectomy on the contour and deformity of the treated breast. The objectives of this study are to determine if a computational model can facilitate the prediction of the breast contour, surface features and tissue density after partial mastectomy, and potentially identify targets for intervention or suggest new procedural modifications to improve cosmetic results. An effective simulation method to predict the surgical outcome of BCT intervention would be useful for the surgeon to ensure a satisfactory cosmetic result and could be a practical tool to aid effective communication with patients.

A novel concept in surgical procedural planning will be used in this study. Wound healing after lumpectomy offers a good model to learn about the mechanism of recovery after internal tissue resection. Physical properties, such as tissue mechanics and gravity, along with biological processes are factors in wound healing. While wound healing has been exhaustively studied in tissues including skin, bone, and embryos, there is very little information about predictive models for healing after surgical resection, particularly for the breast. Currently, no satisfactory animal models exist for BCT, which prompted our initial investigations in human subjects using pre-existing images.

We appear to be the first team working on a computational framework design to predict BCT outcomes. This work is a good example of the converging concepts of computational surgery – <http://www.computationsurgery.org>, and in particular the translation of mathematical modeling into strategies to improve clinical practice. While advances in medical imaging technologies, and informatics have contributed to advances in surgical planning, we propose there is great merit in developing computational models that can quantitatively predict surgical outcomes and offer strategies to optimize surgical procedures.

With the release of sophisticated Finite Element Modeling (FEM) software, breast modeling has been widely investigated in various applications, including biopsy planning and surgery simulation. Azar et al. and Samani et al. proposed a method for guiding clinical breast biopsy based on a deformable FEM of the breast. Tanner et al. presented a method to evaluate the accuracy with which biomechanical models can predict the displacements of tissue within the breast.

Subsequently, research involving breast implants was introduced. Computer simulations for reconstructing the breast have been presented using idealized and realistic geometric models, then subsequently in actual patients. Pamplona et al. have analyzed the impact of stress and

strain occurring in the skin immediately after breast reconstruction. More recent works have focused on predicting the impact of gravity loading on breast mechanics, and reversely, finding the reference state of the breast from the deformed configuration.

In our laboratory, we have performed 3-D virtual surgery using patient MRI data and studied the cosmetic impact of BCT operation. This simulation was restricted to the immediate impact of mechanical tissue removal and may predict the immediate contour result of surgery, not the final shape of the breast after healing and has not been compared to results in actual patients.

### 1.1 Approach to the problem

The immediate impact of tissue removal on breast deformation, as a function of tumor location and size, has been defined by our work using 3-dimensional reconstruction of the breast shape from MRI data taken with patients in a prone position. This approach uses a mechanical model that combines a hyper-elastic model of the soft tissue and a mechanical model of the skin envelope to compute breast deformation as a function of the position of the patient in two consecutive steps: position of the breast at zero gravity and at various gravity loads. From this information, a Graphical User Interface (GUI) is being developed to allow the surgeon to remove tissue in a virtual environment and visualize (or predict) the outcome. Pressures inside the wound will also impact the outcome, so an additional GUI will be developed to simulate changes that occur during treatment (eg, radiation therapy) and healing. In order to confirm the predictive validity of the multiscale model of breast lumpectomy and healing, we plan to study patients who are actively undergoing the surgical removal of breast tissue, treatment for breast cancer, and breast tissue healing.

### 1.2 Rationale for the clinical study

The goal of BCT is to provide a safe therapeutic alternative to total mastectomy while preserving a cosmetically satisfactory and sensate breast. The procedure is less complex and disfiguring than total mastectomy, recovery is more rapid and complications are fewer. A limitation of BCT is that in up to 25% of patients, even lumpectomy, can disfigure the breast. Patients at high risk for deformation include women with relatively small breasts, with volume loss due to previous biopsies, those with high tumor to breast size ratio, and those with tumor positioned in specific areas of the breast – such as those immediately beneath the nipple. Surgeons have recently introduced “oncoplastic” lumpectomy in an effort to move adjacent tissues into the defect created by lumpectomy at the time of initial lumpectomy. This procedure has not been widely embraced given the unpredictable nature of the healing process, and the fact that should positive margins be identified on final pathologic evaluation, the only feasible secondary procedure is total mastectomy rather than re-excision lumpectomy.

However, accurate prediction of breast contour after lumpectomy remains an art rather than a science. The ability to reliably predict breast contour after BCT based on pre-operative imaging and “virtual” surgery would represent a significant improvement in breast cancer patient care. Patients could be fully informed regarding the outcome of surgery and radiation, allowing more evidence-based patient decision-making. Further, for those patients in whom a cosmetic tissue defect will be predicted, a secondary reconstructive procedure would be anticipated – delayed oncoplastic procedures – while still preserving a sensate and natural breast. Breast reconstruction after total mastectomy leaves patients with insensate skin, absence of the nipple-areola complex in most patients, and recovery after these multi-step procedures is much longer than after BCT. Given the equivalence of these two procedures in delivering long-term survival (BCT has been shown to be equivalent to total mastectomy for patients with non-metastatic breast cancer), BCT is clearly a preferred strategy for those women who qualify for the procedure from an oncologic perspective.

The ability to accurately predict breast contour after breast conserving therapy (BCT) for breast cancer could significantly improve patient decision-making regarding the choice of surgery for breast cancer - BCT or mastectomy. As BCT is equivalent to total mastectomy to achieve overall survival in patients with non-metastatic breast cancer, the procedure of BCT offers significant advantages for the 70% of patients who are candidates for this procedure.

## **2 Purpose and objectives**

### **2.1 Purpose**

The purpose of this study is to test the predictive validity of the multiscale model of breast lumpectomy and healing in patients undergoing BCT for breast cancer and identify targets for improvement in BCT.

### **2.2 Objectives**

#### **2.2.1 Primary objective**

The primary objective of this study is to compare the surgical lumpectomy, lumpectomy healing process and surface contour changes to the predicted multiscale model.

#### **2.2.2 Secondary objective**

Secondary objectives are to

- provide information regarding the use of 3-dimensional surface imaging to detect changes over time in the skin surface and dimension related to lumpectomy healing and breast contour
- provide information on the use of ultrasound of the lumpectomy bed and changes that occur during the course of breast cancer treatment and healing
- provide information on thermal imaging and inflammation symptoms
- to describe the course of pain experienced by women undergoing BCT and the correlation of pain to the healing process.

## **3 Design rationale**

The proposed study is a single-center, prospective, pilot observation study to tabulate and measure the changes that occur during treatment and healing for BCT in women with non-metastatic breast cancer for comparison to the multiscale model of breast lumpectomy and healing in order to identify targets for improving BCT.

There is currently no information on which to base a prediction of breast contour following BCT, but the problem of cosmesis following BCT is substantial for many patients. The data collected in this observational study will provide a basis for testing the predictability of the multiscale model of breast lumpectomy and healing.

## 4 Experimental plan

### 4.1 Study design

This is a single-center, prospective, pilot observation study. Eligible subjects who enroll in this study will begin at the time of informed consent, which will occur during the pre-operative, surgical evaluation time.

The study plan demonstrates when subjects will have their surgery and when subjects will have study visits (Figure 1). The planned procedures are detailed in section 5 and the schedule of events table in section 6.

[figure not shown]

**Figure 1. Study design.**

#### 4.1.1 Study endpoints

The primary endpoint of this study is the comparability of the surgical/healing outcome of the lumpectomy and breast surface contour to the predicted changes from the multiscale model. A mean combined score  $\geq 60\%$  agreement will be considered acceptable in this pilot project.

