##### 4.1.1.1 Primary variables

The primary variables will be surface contour captured by the 3-dimensional 180° camera, lumpectomy dimensions captured by ultrasound, predicted surface contour and predicted lumpectomy dimensions from the multiscale model.

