## **6.4 3-Dimensional Surface Imaging of the Breast**

A 3-dimensional 180° camera will be used to capture surface imaging prior to surgery and at three time-points after surgery (visits 2, 4 and 6). The surface imaging will provide measures of breast deformity.

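### The protocol does not fix whether breast contours or contour changes are scored against the model, and plans no check of the model's unoperated shape against the pre-operative 3-D image

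*Protocol*

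**What the plan says.** Four places describe what is compared, and they do not agree:

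- Protocol 2.2.1 (primary objective) is to "compare the surgical lumpectomy, lumpectomy healing process and surface contour changes to the predicted multiscale model", so the measured side is a change.
- Protocol 4.1.1 (primary endpoint) is the "comparability of the surgical/healing outcome of the lumpectomy and breast surface contour to the predicted changes from the multiscale model". An observed outcome and contour are set against predicted changes, and a mean combined score of at least 60% is acceptable.
- Protocol 4.1.1.1 (primary variables) names the contour captured by the camera and, on the model side, "predicted surface contour and predicted lumpectomy dimensions from the multiscale model". Both sides are levels.
- Protocol 7.1.3 (quantitative primary outcome) is a combined score of correlations between three measured processes and their predictions. One process is change in surface contour. The 60% criterion is repeated, with assessment at weeks 10 and 26.

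On the origin of the prediction, Protocol 1.1 describes "3-dimensional reconstruction of the breast shape from MRI data taken with patients in a prone position", followed by two computed steps, "position of the breast at zero gravity and at various gravity loads". Section 1 says of the existing simulation that it "has not been compared to results in actual patients".

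On the available data, Protocol 6.4 says that the "camera will be used to capture surface imaging prior to surgery and at three time-points after surgery". The schedule in 6.8.1 puts these images at visit 1 and at weeks 1, 6 and 24. Their stated use is to measure breast deformity. The protocol names no comparison of the model's pre-operative shape with the visit-1 image.

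**The concern.** The study exists to find out whether the model predicts what lumpectomy and healing do to the breast (Protocol 2.1). A prediction that starts from a prone MRI and is carried by computation to another position can be wrong before any tissue is removed. If post-operative contour is scored directly against predicted contour, that pre-existing error is mixed with the error of interest. A low score might then reflect only the gravity step. A high score might reflect only that a large breast was predicted to be large and a small one small.

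The visit-1 3-D image could separate the two, because it shows the unoperated breast in the camera's own setting. At stake is the meaning of the single pass mark, 60%, in a study of 12 evaluable women.

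**Working it through.** **Inputs from the protocol.** The only figure bearing on the score is the 60% criterion (4.1.1, 7.1.3). The enrolment figure reproduces (12 evaluable + 3 replacements = 15; 4.1.2, 7.1.1) but has no bearing here. No standard deviation, agreement formula, size of conversion error or camera posture is given, so what follows is an illustration on assumed inputs.

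**Set-up (assumed).** Take one contour summary per woman:

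- B: her own anatomy, between-woman SD sB.
- D: true change from surgery and healing, SD 1 (the unit).
- P: the model's predicted change, SD 1, with correlation rho to D.
- e: conversion error already present before surgery, SD sE.
- B and e are independent of each other and of D and P; errors have mean zero.

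Measured post-operative contour is B + D. Modelled post-operative contour is B + e + P.

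**Four possible scores.**

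1. Distance between levels: RMS = sqrt(sE² + 2(1 − rho)).
2. Correlation of levels: (sB² + rho) / sqrt((sB² + 1)(sB² + sE² + 1)).
3. Measured change against (model after surgery minus *measured* baseline): rho / sqrt(1 + sE²).
4. Measured change against the *model's own* change: rho, because e cancels.

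**Results.**

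| Score | Inputs | Result |
|---|---|---|
| 1 | rho 0.8, sE 0 | sqrt(0.4) = 0.63 |
| 1 | rho 0.8, sE 1 | sqrt(1.4) = 1.18 |
| 2 | rho 0.8, sB 1, sE 0 | 1.8/2 = 0.90 |
| 2 | rho 0.8, sB 1, sE 1 | 1.8/sqrt(2 × 3) = 0.73 |
| 2 | rho 0, sB 1, sE 1 | 1/sqrt(2 × 3) = 0.41 |
| 2 | rho 0, sB 3, sE 1 | 9/sqrt(10 × 11) = 0.86 |
| 3 | rho 0.8, sE 0.5 | 0.8/sqrt(1.25) = 0.72 |
| 3 | rho 0.8, sE 1 | 0.8/sqrt(2) = 0.57 |
| 3 | rho 0.8, sE 1.5 | 0.8/sqrt(3.25) = 0.44 |
| 4 | rho 0.8, any sE | 0.80 |

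Under score 3, a true 0.80 falls below 0.60 once sE exceeds sqrt((0.8/0.6)² − 1) = 0.88.

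Under score 2, a model with rho = 0 passes 0.60 once anatomy varies enough. With sE = 1 and x = sB², the condition x/sqrt((x + 1)(x + 2)) = 0.6 gives 0.64x² − 1.08x − 0.72 = 0. Hence x = 2.20 and sB is about 1.5.

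**Reading.** The same model can pass or fail according to which of the protocol's wordings is followed. Conversion error worsens scores 1 to 3. Shared anatomy raises score 2 regardless of skill. Only score 4 is free of both, and only for error that is additive.

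**The case against.** The strongest reply is that most of the wording already points to change. The objective and the quantitative outcome say so, the endpoint sets the outcome against predicted changes, 7.1.2 refers to changes from baseline, and a pre-operative image is scheduled. Section 4.1.1.1 may merely list what the instruments record. This largely stands. A reader might infer that post-operative contour is definitely scored without a baseline and that conversion error will count as failure to predict surgery. The documents do not support that: it follows only on the level reading or if just the measured baseline is subtracted, and the direction depends on the metric. Even so, the change wording supplies a baseline for the measured side only. The predicted change is nowhere defined.

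Second, the scoring formula may sit in an SAP that is not shown. That is fair for the formula. It does not cure the disagreement among the protocol's own primary objective, endpoint, variables and outcome.

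Third, for the use foreseen in 1.2, informing a woman of her likely contour from pre-operative images, conversion error is genuine prediction error. This stands. Total-contour agreement is a legitimate result, and a differenced score alone could flatter the tool.

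Fourth, 1.1 describes the prone MRI in the context of work already done. The inclusion criterion gives no MRI posture, and the camera posture is not stated either. This too stands, and is why no size can be attached to the error.

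Fifth, the tissue model is hyper-elastic, so conversion error need not cancel on subtraction. This stands as a limit of differencing, and is a reason to report the pre-operative agreement as well.

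**Conclusion.** The point holds as an inconsistency with a cheap remedy. The protocol uses contour and contour change interchangeably across its primary definitions, and it names no check of the model's unoperated shape against the visit-1 image. If levels are scored, the 60% criterion cannot be read as skill in predicting surgery and healing. On assumed inputs, a correlation of levels reaches 0.86 with no such skill, while a partly corrected change score turns a true 0.80 into 0.57.

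These figures depend on assumed relative SDs, independence and additive error. They show that the choice matters, not how large the real error is. It would also go too far to conclude that the study says nothing about breast conserving therapy: on a change-against-model-change reading the additive part of the problem disappears, and the total-contour score answers a real clinical question. This should be settled before analysis; it does not undermine the pilot's design.

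**What to change.** - In Protocol 4.1.1, 4.1.1.1 and 7.1.3, use one definition of the contour component, consistent with 2.2.1. Measured side: 3-D image at the visit minus the visit-1 image. Predicted side: model at that visit minus the same model with no resection.
- State which 3-D visit feeds each scored time point, since 7.1.3 assesses at weeks 10 and 26 while the images are scheduled at weeks 1, 6 and 24.
- For each woman, run the model with no resection, score it against her visit-1 3-D image, and report that agreement beside the post-operative score.
- Keep total-contour agreement, if wanted, as an additional result labelled as such.

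The cost is one extra model run per woman (at most 15), alignment of surfaces across visits, and wording. No visit or image is added. Differencing removes only additive error, so the no-resection agreement should be reported even when the change score looks good.

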#### 4.1.2 Number of subjects

Up to 15 de novo breast cancer subjects will be enrolled in order to allow for early drop-outs resulting in 12 evaluable cases.

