## 7 Statistical analysis plan

### 7.1.1 Sample size

This single-center study will enroll up to 15 de novo breast conserving therapy subjects. This is a prospective, pilot, observational study. Subjects withdrawn from the study cannot re-enter. Up to 3 patients, if withdrawn prior to week 6, will be replaced. Twelve subjects will be considered

evaluable if they complete up to visit 5 and will be considered completers if they complete all study visits and procedures.

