### 7.1.3 Evaluation criteria:

- The primary outcome measure will be
- Qualitative:
  - confirmation that relative size of the lumpectomy to the breast, tissue composition ratio of fat versus glandular, and location of the tumor will provide a qualitative grading of the potential cosmetic outcome.
  - correlation of the wound edge shape to mechanical stress
  - correlation of volume loss due to healing to cosmesis outcome.
- Quantitative: a combined score of the correlation between three measured processes (lumpectomy dimensions, lumpectomy healing process, surface contour changes) and the predicted outcomes from the multiscale model measured/assessed at weeks 10 and 26 postsurgery with a mean accuracy rate of  $\geq 60\%$ .
- Secondary outcome measures will include postsurgery:
  - the proportion of subjects experiencing pain  $\geq 8$  on more than one measurement post operatively and the relationship of pain to the accuracy of the multiscale model
  - the proportion of subjects experiencing increased pain ( $\geq 3$  unit increase) pre to post ultrasound at each visit to determine the possible invasiveness of these multiple post-surgery ultrasounds
  - detection of changes in the thermal image of the breast tissue related to inflammation and healing
  - the summary of the independent judgment (Harvard/NSABP/RTOG scale score) of cosmesis taken at weeks 10 and 26

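### The 60% acceptance rule averages three processes with no minimum for surface contour and no benchmark, so a model that fails on contour can still be called acceptable

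*Protocol*

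**What the plan says.** Section 4.1.1 makes the primary endpoint the comparability of the observed lumpectomy, healing and surface contour with the model's predictions. A mean combined score of at least 60% "agreement will be considered acceptable in this pilot project".

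Section 7.1.3 gives the quantitative primary outcome as "a combined score of the correlation between three measured processes (lumpectomy dimensions, lumpectomy healing process, surface contour changes", each set against the model's predicted outcome. It is to be "measured/assessed at weeks 10 and 26 postsurgery with a mean accuracy rate of" at least 60%. One threshold is thus described as agreement, as correlation and as an accuracy rate.

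Section 4.1.1.1 lists two kinds of observed primary variable, "surface contour captured by the 3-dimensional 180° camera, lumpectomy dimensions captured by ultrasound", together with their predicted counterparts.

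No section states weights, a minimum for any component, a comparator or a reason for 60%. On sample size, Section 4.1.2 says that up to 15 "subjects will be enrolled in order to allow for early drop-outs resulting in 12 evaluable cases".

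**The concern.** Contour prediction is why the study exists. The background and Section 1.2 present reliable prediction of breast contour as the advance that would help women choose between breast conserving therapy and mastectomy. Section 2.1 gives the purpose as testing the model's predictive validity.

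A mean without a floor lets good scores on cavity size and healing cover a poor score on contour. Without a comparator, a pass also does not show that the model predicts contour better than assuming the breast stays as it was before surgery. The study could report the model as acceptable when the part that matters to patients has failed, and a reader would take the pass as support for it.

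**Working it through.** **The plan's own arithmetic.** Section 7.1.1 says "Up to 3 patients, if withdrawn prior to week 6, will be replaced". 12 evaluable + 3 replacements = 15, which agrees with Section 4.1.2. The 60% cannot be reproduced, because the protocol gives no null value, variability, error rate or other input for it.

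**How low contour can score and still pass.** Inputs: threshold 60% (Sections 4.1.1 and 7.1.3) and three processes (Section 7.1.3). Assumption: the combined score is their equally weighted mean. If the other two processes each score *a*, the lowest passing contour score is 3 × 60 − 2*a* = 180 − 2*a*.

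| Other two processes, each | Lowest passing contour score |
|---|---|
| 80% | 180 − 160 = 20% |
| 85% | 180 − 170 = 10% |
| 90% | 180 − 180 = 0% |

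Check: (90 + 90 + 0)/3 = 60.

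**Sensitivity to the weights.** Let contour have weight *w* and the rest average *o*. A contour score of zero passes if (1 − *w*) × *o* ≥ 60. As *o* cannot exceed 100, this is possible whenever *w* ≤ 40%. If only the two kinds of variable in Section 4.1.1.1 counted, at half weight each, the lowest passing contour score would be 120 − *o*: 30% when dimensions score 90%, and 20% when they are perfect. The weakness shrinks with more weight on contour but does not go away.

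**A benchmark, on one reading only.** Section 1.2 says that "in up to 25% of patients, even lumpectomy, can disfigure the breast". Suppose contour were scored as right or wrong per patient on whether the breast is deformed. A constant guess of no deformity would then be right in at least 1 − 0.25 = 75%. Since 0.60 × 12 = 7.2, the smallest passing count is 8 (7/12 = 58.3%, 8/12 = 66.7%). With X binomial:
- P(X ≥ 8 | 12, 0.75) = 0.84;
- P(X ≥ 8 | 12, 0.80) = 0.93, taking a 20% deformity rate as an assumption within the stated upper limit.

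The guess has expected accuracy above 60% at any deformity rate below 40%.

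**Why this does not carry over to the composite.** The guess says nothing about dimensions or healing. With contour at 75% and the other two at zero, the equally weighted score is 75/3 = 25%, a fail. The other two would have to average (180 − 75)/2 = 52.5% for a pass. If the score is a correlation, a constant guess has no defined value.

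**Where contour is measured.** Sections 6.4 and 6.8.1 place 3-D imaging before surgery and at visits 2, 4 and 6, which are weeks 1, 6 and 24. Section 7.1.3 assesses the score at weeks 10 and 26. No 3-D scan is scheduled at week 10; the nearest to week 26 is visit 6.

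**The case against.** The strongest reply is that the 60% is a modest pilot mark with no treatment or go/no-go decision tied to it, and that it is not the only evidence on the model. Section 7.1.2 plans ROC curves, on which a constant prediction would show no discrimination. Section 6.8 adds independent judging of cosmesis. The metric, the weights and separate reporting of components may also be set in a statistical analysis plan that is not shown. All of this is fair, and it limits the seriousness of the point. It does not remove it: the ROC and cosmesis analyses are not part of the acceptance rule, and the protocol itself fixes that rule as a mean of at least 60%.

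The 90/90/0 case is a boundary example. It shows what the rule permits and does not forecast what the model will score.

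Two stronger readings are tempting, and the protocol supports neither:

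- A reader might infer that 60% lies below what a guess of no deformity achieves. The 75% comes from a per-patient disfigurement rate in the background text, while the 60% applies to a three-part score that is also called a correlation. No section scores contour as deformed or not deformed.
- A reader might infer that ultrasound supplies two thirds of the score. Section 6.7 says that healing is assessed with the thermal camera, Section 4.1.1.2 makes thermal data secondary, and Section 2.2.2 links ultrasound to healing. The source of the healing component is therefore unclear, and the fraction also needs equal weights.

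**Conclusion.** The point holds in this form: the acceptance rule has no contour minimum and no benchmark, so it can be met by a model that fails on contour. Under equal weights, a contour score of 0% passes when the other two reach 90%, and 20% passes when they reach 80%. A zero on contour can pass for any contour weight up to 40%. These figures assume that the combined score is a weighted mean on a 0 to 100% scale, which is the natural reading of the text but is not spelled out.

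The 60% has no stated basis. Whether a trivial prediction would reach it is not established; the 75% comparison holds only for a right-or-wrong contour score per patient. The rule should be changed before the result is interpreted, but the study's data collection remains sound for the purpose.

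**What to change.** In Sections 4.1.1 and 7.1.3:

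1. Report the scores for dimensions, healing and contour separately, next to any average.
2. Do not call the model acceptable on the average alone. Require the contour component to reach the protocol's own 60%.
3. Take the visit 1 pre-operative 3-D scan as a no-change prediction. Score it and the model with the same contour metric, in the same women, at the scheduled post-operative scans, with visit 6 (week 24) as the main comparison. Report the paired difference, model minus no change, with its 95% CI. The metric should be one of agreement or distance, since a correlation of changes is undefined for a prediction of no change.
4. Tie the contour assessment to visits at which a 3-D scan exists, as none is scheduled at week 10.

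The cost is in analysis and wording only; no visit, scan or patient is added. The criterion becomes harder to meet. With 12 women the interval will be wide, and fewer may contribute at visit 6, because Section 7.1.1 counts a woman as evaluable once she has completed visit 5. The difference should therefore be read as an estimate, not as a test that the study is sized to pass.
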